### 2.12. Sample Size

The sample size was calculated based on our own retrospective data and literature. In pilot screening, we detected ILD changes in 13 of 73 (18%) asymptomatic, at-risk relatives, while in the literature, ILD changes were seen in 16–23% of the HRCT-scans [15,18,19,57]. In the present study, we will include 200 participants, with an expected ratio of 37 participants with the presence of ILD changes and 163 participants with the absence of ILD changes at HRCT scan.

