### 2.13. Statistical Analysis

Categorical variables, including presence/absence of Velcro-like crackles, presence/absence of clubbing, MRC dyspnea scale, and *MUC5B* rs35705950 genotype will be expressed as numbers with percentages. Continuous variables, including FVC, TLC, DLCO (corrected for hemoglobin), VAS Cough score, MMP7 level, CCL18 level, KL-6 level, SP-D level, and 6MWT (distance in meters, sat O2 rest, sat O2 after 6MWT, sat O2 nadir, and sat O2 rest minus sat O2 nadir) will be displayed as means with standard deviations or medians with standard error, where appropriate.

The primary objective will be tested using a chi-square test or Fisher-exact test (as appropriate for categorical variables) and Student’s *t*-test or Mann–Whitney U test for continuous variables. Univariate logistic regression will be used to test which parameters differ between the groups. Parameters that are found to be diagnostic in univariate analysis with *p* < 0.20, will subsequently be assessed in a multivariate logistic regression analysis using the backward method to determine which are the strongest predictors for ILD changes on HRCT scan at baseline. In case too many parameters meet the *p* < 0.20 criterion, a cut-off of *p* < 0.10 will be used.

The secondary objective will be tested using the paired *t*-test, or Wilcoxon signed-rank test for the differences between the groups, and a repeated measure ANOVA test for the differences within the same group over time. After year 2, linear mixed models will be used to determine the strength of change of the parameters over time within and between both groups.

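### Selecting predictors by a p<0.20 filter, a results-dependent switch to p<0.10 and backward elimination, with at least 17 parameters and about 37 cases, is likely to keep noise and drop real markers

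*Protocol article*

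**What the plan says.** Section 2.13 (Statistical Analysis) of the protocol article gives the primary objective two layers. Each parameter is first compared between participants with and without ILD changes, and univariate logistic regression is run. Parameters with p<0.20 "will subsequently be assessed in a multivariate logistic regression analysis using the backward method to determine which are the strongest predictors" of ILD changes at baseline. The threshold can then move: "In case too many parameters meet the" p<0.20 criterion, p<0.10 applies instead. The article does not say how many is too many, and it gives no removal level for the backward step.

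The same section names 4 categorical parameters, 8 continuous ones outside the walk test and 5 walk-test measures. The last of these include "sat O2 nadir, and sat O2 rest minus sat O2 nadir" as well as resting saturation itself. The lists are introduced as examples. Table 1 adds blood count, kidney and liver tests, EQ-5D and FAS.

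On size, Section 2.12 states "In the present study, we will include 200 participants", "with an expected ratio of 37 participants with the presence of ILD changes and 163 participants" without. The Discussion says what the result is for: choosing who needs an HRCT scan, and possibly removing uninformative parameters from clinical screening.

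**The concern.** The outcome is used twice, once to filter the parameters and once to eliminate among those that passed. The number of cases is small for the number of parameters examined. Under these conditions, which parameters survive depends heavily on chance. A noise parameter that passes a loose filter has a fair chance of staying, and a real parameter of moderate strength can easily be lost.

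Both errors bear on the uses named in the Discussion. A noise parameter could be carried into screening as a predictor. A useful one could be dropped because it failed to survive in one sample with 37 cases.

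**Working it through.** **The plan's own figure.** "In pilot screening, we detected ILD changes in 13 of 73 (18%) asymptomatic, at-risk relatives" gives 200 × 13/73 = 35.6 expected cases. The 16–23% from the literature gives 200 × 0.16 = 32 to 200 × 0.23 = 46. The stated 37 (37/200 = 18.5%) fits both. The article gives no alpha, power or effect size, so there is no power figure to reproduce.

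**Cases per parameter.** 4 + 8 + 5 = 17 named parameters.
- 37/17 = 2.2
- 32/17 = 1.9 and 46/17 = 2.7 over the literature range

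**Hand check.** Assumptions: three real parameters with standardized mean difference 0.5, 14 noise parameters, all independent, 37 cases and 163 non-cases.
- Power of a single real parameter is 0.93 at p<0.20, 0.86 at p<0.10 and 0.78 at p<0.05.
- Expected number passing p<0.20: 14 × 0.20 + 3 × 0.93 = 5.6. At p<0.10: 14 × 0.10 + 3 × 0.86 = 4.0.
- Chance that at least one noise parameter stays, taking the removal level as the error rate for each: 1 − 0.95^14 = 0.51 at 0.05, and 1 − 0.90^14 = 0.77 at 0.10.
- Chance that all three real ones stay is at most about 0.784^3 = 0.48 at 0.05 and 0.8645^3 = 0.65 at 0.10, before the cost of fitting them jointly with noise.

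**Simulation of the full sequence.** The same assumptions were used with normally distributed parameters: univariate logistic filter, then backward logistic elimination. The main run had 1,500 studies per setting, with AUC also computed in 10,000 new subjects. Ranges show repeat simulations of the same setting.

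| Three real + 14 noise, filter p<0.20 | Removal 0.05 | Removal 0.10 |
|---|---|---|
| At least one noise parameter kept | 52–53% | 74–77% |
| All three real parameters kept | 38–40% | 55–56% |
| Noise as share of kept parameters | 25% | 35% |
| AUC, apparent / new data | 0.75 / 0.68 | 0.76 / 0.68 |

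**Sensitivity.**
- Filter at p<0.10 throughout: noise kept in 45–48% (removal 0.05) or 64–67% (removal 0.10). All three real parameters kept in 38% or 54%. Optimism in AUC is still about 0.07.
- One stronger real parameter (0.8, 0.5, 0.5): noise kept in 50% or 72%, optimism 0.05–0.06.
- Six real parameters (0.4–0.6) with correlated blocks (r 0.3–0.7): noise kept in 44% or 56%, AUC 0.80 against 0.73 or 0.81 against 0.74.

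**Linear dependence.** Resting saturation, nadir saturation and their difference are three columns of rank 2. They cannot all be in one model.

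**The case against.** The best counter-argument is that this is a condensed article. Internal validation, shrinkage, the removal level and the final candidate list may all be in a full protocol or SAP that is not shown. That stands. A reader might infer that the study has no optimism correction, but the document does not support this, and the point does not rest on it. It rests on the filter, the movable cut-off and the backward step, which the article itself fixes. Bootstrapping elsewhere would reveal the instability but not remove it.

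A reader might also infer that the plan will report inflated accuracy. Section 2.13 promises no AUC, sensitivity or specificity; its stated aim is to identify predictors. The AUC figures therefore apply only to performance measures that someone later takes from the selected model.

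Further objections, and what remains of each:
- The 17 parameters appear in sentences about descriptive summaries. Reading them as the candidate set is reasonable but inferred. Larger counts have no itemized list behind them and are not used here.
- Pure-noise scenarios give more striking figures, but Sections 2.6, 2.7 and 2.9 cite earlier associations in relatives for lung function, MMP7, SP-D and MUC5B. The scenario with real predictors is the fair one.
- The cut-off moves only in the stricter direction and is announced in advance. What remains is that its trigger is undefined and depends on the results.
- Only about 5.5 parameters reach the joint model, or 37/5.54 = 6.7 cases each. But the filter has already used the outcome on all 17.
- The dependence among saturation measures matters only if all three pass. Any two give the same fit, so only the label of the survivor is arbitrary. This is minor.
- Univariate comparisons are also planned, so the backward model is not the only output for the primary objective.

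**Conclusion.** The concern holds as a likely outcome, not a certain one. With about 2.2 cases per named parameter, the selection procedure in Section 2.13 is likely to keep noise and to lose real markers. In the main scenario at least one noise parameter is kept in about 50–77% of studies, and all three real ones in about 40–55%. With correlated parameters and six real ones the noise figure is 44–56%, so the problem shrinks but does not disappear. The p<0.10 fallback lowers the noise figure by roughly 4 to 10 percentage points and does not help retain real parameters. Optimism in AUC is about 0.05–0.08 across these settings.

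These sizes rest on assumed effect sizes, assumed removal levels of 0.05 and 0.10, normally distributed parameters and, except in the last sensitivity setting, independence. The direction does not depend on the exact values. This should be fixed before the baseline model is fitted. It does not invalidate the study, and the univariate comparisons are unaffected.

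**What to change.** Preferred: remove the univariate filter and the switch between p<0.20 and p<0.10. Fix a reduced candidate list before looking at the outcome, for example with one desaturation measure instead of three dependent ones, and fit one penalized logistic model. The list should be short. As a guide, take a target shrinkage of 0.9 and an assumed Cox–Snell R² at 30% of its maximum. Then 4 parameters need about 174 participants (32 cases) and 8 need about 348. At 15% of the maximum, 4 already need about 369.

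If backward selection is kept: state one fixed entry threshold and one removal level, and repeat the whole filter-plus-selection sequence in bootstrap samples (at least 500). Report selection frequencies and optimism-corrected performance beside the selected predictors. If an unseen SAP already does this, a cross-reference in the text is enough for that part.

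Cost: revised analysis wording and some computing time. There are no new data, visits or participants. The reported performance will look less favourable, and the ranking of predictors will be presented with more caution.

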## 2. Materials and Methods

### 2.1. Objectives and Endpoints

The primary objective of the FLORIS study is to determine the diagnostic value of parameters for early disease detection in first-degree relatives of patients with FPF. To this end, the presence or absence of ILD changes on a baseline HRCT scan (see Figure 1) will be used to determine the predictive value for early disease of a set of clinical and exploratory parameters (see Table 1).

As secondary objectives, the study aims to gain insight into the natural history of FPF and to determine the necessary interval between screening visits. Secondary endpoints will assess the change in parameters between baseline and follow-up after one and two years within each group separately, and analyze differences between the groups with and without ILD-changes (see Figure 1).

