### 2.4. Assessment of Preclinical ILD

At baseline, subjects will be stratified into two groups based on the presence (ILD changes group) or absence (no ILD changes group) of ILD changes on HRCT scan (Figure 1). ILD changes are defined as extensive disease, familial interstitial lung abnormalities (FILA) or minimal FILA (see Box 1). The definition of FILA is based on the position paper of the Fleischner Society on interstitial lung abnormalities (ILA) [21]. The position paper does not consider abnormalities identified during screening for ILD in high-risk groups, including familial ILD, as ILAs because they are not incidental. The Society suggests the term preclinical ILD for such cases, however, this suggests that subjects have ILD which is not always the case. Therefore, we added familial (F) to refer to the context of the findings, which together makes FILA. To define all possible abnormalities during screening, minimal FILA will be defined as FILA in less than 5% of the lung zone (see Box 1).

A thoracic radiologist will assess the HRCT scan. All the findings of study visits will be discussed with an expert pulmonologist in the field and, when necessary, in a multidisciplinary discussion. If ILD changes or other abnormalities in clinical parameters are found that warrant evaluation, participants will remain in the study, but will also be referred to regular care for examination by a general practitioner or pulmonologist.

Box 1Definition of ILD changes in the FLORIS study.ILD changes on HRCT scan in first-degree family members of FPF patients are defined as:
Extensive disease: non-trivial abnormalities present in three or more lung zones (a)FILA: Any of the following non-dependent abnormalities involving >5% of a lung zone: traction bronchiectasis, honeycombing, ground-glass or reticular abnormal-ities, lung distortion and non-emphysematous cysts (a)Minimal FILA: Any of the following non-dependent abnormalities involving <5% of a lung zone: traction bronchiectasis, honeycombing, ground-glass or reticular abnormalities, lung distortion and non-emphysematous cysts
(a) Concepts are based on the definition of ILA by Hatabu et al. [21] for incidental findings and adjusted to a screening setting of high-risk relatives

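### The between-group comparison in the secondary objective is assigned paired tests, although the two groups are unmatched people of unequal number

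*Protocol article*

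**What the plan says.** Section 2.1 lists what the secondary endpoints cover: "change in parameters between baseline and follow-up after one and two years within each group separately, and analyze differences between the groups". There are thus two contrasts: change within a group, and the difference in change between groups.

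The groups are formed once, from the first HRCT scan, as set out in section 2.4: "subjects will be stratified into two groups based on the presence (ILD changes group) or absence (no ILD changes group) of ILD changes". Section 2.12 states how large they should be: "expected ratio of 37 participants with the presence of ILD changes and 163 participants with the absence of ILD changes at HRCT scan".

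Section 2.13 then allocates the tests for the secondary objective. It names the paired t-test as the first option and continues: "Wilcoxon signed-rank test for the differences between the groups, and a repeated measure ANOVA test for the differences within the same group". The sentence that follows adds linear mixed models after year 2, covering change both inside each group and between the two.

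For the primary objective, which compares the same two groups at baseline, section 2.13 names unpaired tests for continuous variables: Student's t-test or the Mann–Whitney U test.

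**The concern.** A paired t-test or Wilcoxon signed-rank test works on differences within pairs, such as one person at two visits or two people matched by design. Section 2.13 attaches these tests to a comparison of two sets of different, unmatched people. The section treats the same two groups as independent for the primary objective and as paired for the secondary one.

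A stated secondary endpoint therefore has a named test that cannot be carried out. The longitudinal comparison is what the Discussion relies on to judge whether yearly screening is needed and how lung function changes in early disease. If the test has to be replaced at analysis, the replacement is chosen after the data can be seen, whereas the Discussion presents advance description of the protocol as a safeguard against bias. The exposure is greatest for any comparison made at year 1, where no other between-group test is named.

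**Working it through.** **1. The plan's own split.** Inputs from section 2.12: 200 participants; in the pilot, "we detected ILD changes in 13 of 73 (18%) asymptomatic, at-risk relatives"; in the literature, "ILD changes were seen in 16–23% of the HRCT-scans".

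- Pilot rate: 13/73 = 17.8%, and 200 × 13/73 = 35.6.
- Rounded pilot rate: 200 × 0.18 = 36.
- Literature range: 200 × 0.16 = 32 to 200 × 0.23 = 46.
- The stated split: 37/200 = 18.5%, leaving 200 − 37 = 163.

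The split of 37 and 163 is consistent with the cited rates. At any prevalence in the cited range the groups are unequal.

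**2. Can the named test be run?** A paired test needs n pairs (x_i, y_i) and analyses d_i = x_i − y_i. With 37 values in one group and 163 in the other, no rule in the article says which x belongs to which y. Standard software (Python's scipy) was given vectors of 37 and 163 values. It rejected both the paired t-test and the signed-rank test because the lengths are incompatible.

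**3. Which named method serves which contrast (section 2.13)?**

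| Contrast | Method named | Fits the data structure? |
|---|---|---|
| Between groups, baseline | Student's t or Mann–Whitney U | Yes |
| Between groups, follow-up | Paired t or Wilcoxon signed-rank | No |
| Within group, over time | Repeated-measures ANOVA | Yes |
| Within and between, after year 2 | Linear mixed model | Yes |

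Only the second row fails. For a comparison made at year 1 it is the only between-group row available.

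**4. Illustrative size.** The article states no significance level or power for this objective. Two-sided 5% and 80% power are assumed here, and participants are treated as independent. In SD units of the change score, by normal approximation:

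detectable difference = (1.960 + 0.842) × √(1/n₁ + 1/n₂)

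- Unpaired, 37 vs 163: 2.802 × √(1/37 + 1/163) = 2.802 × 0.182 = 0.51 SD. The t-based calculation also gives 0.51.
- 37 forced pairs with no correlation: 2.802 × √(2/37) = 2.802 × 0.232 = 0.65 SD. The t-based calculation gives 0.473 SD of the paired difference, and 0.473 × √2 = 0.67 SD.
- Participants discarded by forcing pairs: 163 − 37 = 126, which is 126/200 = 63% of the cohort and 126/163 = 77% of the group without ILD changes.

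Power under the same assumptions:

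| True difference | Unpaired, 37 vs 163 | 37 forced pairs |
|---|---|---|
| 0.3 SD | 38% | 25% |
| 0.5 SD | 78% | 58% |
| 0.6 SD | 91% | 73% |

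**The case against.** The strongest reply is that the next sentence of section 2.13 already supplies a valid analysis. A linear mixed model needs no pairs and handles groups of 37 and 163. Follow-up ends at year 2, so this is the analysis of the complete data. That stands. A reader might infer that the between-group change results as a whole would be invalid or would lose most of the data, and the article does not support this. What remains is that the objective is said to be tested with the paired tests and the ANOVA. The mixed model is added after year 2 and is not said to replace them.

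A second reply is that this is a slip, with paired tests meant for baseline-to-follow-up change within a group. That is the likeliest explanation, but the text does not say so. Simply swapping the two assignments would not be enough either: a repeated-measures ANOVA compares groups only if it contains a between-subject group factor, and none is stated.

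A third reply is that a test that will not run cannot mislead anyone. This is largely right. A reader might also infer wrong standard errors and p-values from arbitrary pairing. Pairing unrelated to outcome leaves the paired t-test valid and merely wastes data, and nothing in the article suggests that pairs would be formed. The forced-pairs figures above are therefore illustrative and do not forecast what will happen.

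Two further criticisms might be drawn from the same paragraph, and neither is upheld. Losses from missed visits under repeated-measures ANOVA cannot be sized, because the article gives no missed-visit rate. Longitudinal models for crackles, clubbing and the MRC scale are detail that a condensed article may leave to a fuller plan.

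Finally, some participants may be related to one another, since patients can pass study letters to their family. That may weaken strict independence between the groups, but it does not create one-to-one pairs.

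**Conclusion.** The point holds in a limited form. Section 2.13 names paired tests for a comparison of unmatched groups, expected to number 37 and 163, so that test cannot be computed as written. This is an error in a stated rule and does not depend on what a separate analysis plan might add. It affects the simple between-group comparisons of the secondary objective, above all any made at year 1. The primary analysis is untouched, and the mixed model after year 2 remains valid for the complete data.

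The illustrative gap, 0.51 SD unpaired against 0.65 to 0.67 SD with forced pairs, rests on four assumptions: two-sided 5%, 80% power, independent participants and uncorrelated pairs. The finding itself rests on none of them; it follows from the group definition and the wording of section 2.13.

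**What to change.** Rewrite the secondary-objective paragraph of section 2.13 as follows:

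- **Main analysis.** A linear mixed model with group, time, group-by-time and a participant random effect. The group-by-time term is the between-group comparison of change.
- **Simple between-group comparisons at year 1 or year 2.** Unpaired tests (t-test or Mann–Whitney U) on change from baseline, in line with the tests already named for these groups at baseline.
- **Within-group change between two visits.** Paired t-test or Wilcoxon signed-rank test.

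State that the mixed model takes precedence over the simple tests. The cost is one paragraph of analysis wording, with no new data and no change to visits or sample size. It should be made before any year-1 comparison is run.

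### The secondary analysis names paired tests for a comparison between two unmatched groups of different people; the planned mixed model covers this only in part

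*Protocol article*

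**What the plan says.** Section 2.1 (Objectives and Endpoints) sets the secondary endpoints as change in the parameters from baseline to one and two years, to be assessed "within each group separately, and analyze differences between the groups with and without ILD-changes". Two questions are asked: how each group changes, and whether the groups differ.

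Section 2.13 (Statistical Analysis) then assigns the tests. It offers the paired t-test first and continues with its rank-based counterpart: "Wilcoxon signed-rank test for the differences between the groups, and a repeated measure ANOVA test for the differences within the same group over time". The sentence after that adds: "After year 2, linear mixed models will be used to determine the strength of change of the parameters over time within and between both groups".

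Section 2.4 defines the groups from the baseline scan: "subjects will be stratified into two groups based on the presence (ILD changes group) or absence (no ILD changes group) of ILD changes on HRCT". Section 2.12 gives "an expected ratio of 37 participants with the presence of ILD changes and 163 participants with the absence of ILD changes at HRCT scan".

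For the primary objective, which compares the same two groups at baseline, section 2.13 names Student's t-test or the Mann–Whitney U test for continuous variables.

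**The concern.** The paired t-test and the Wilcoxon signed-rank test both work on a single set of differences, one per unit. They suit the same person at two visits, or matched pairs. A participant is in one group or the other according to the baseline scan, so no unit contributes a value to both groups, and no section describes matching. The tests attached to the between-group comparison do not answer that question.

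This is not detail left to a fuller document. The article states a method, and the method does not fit the comparison.

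The Discussion says that the longitudinal data should show whether yearly screening is needed and how lung function changes in early disease. A comparison of change between the groups bears on both. If the sentence stays as it is, the replacement test would be chosen after the data are in hand.

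**Working it through.** **1. The plan's own figure.** Section 2.12 gives 13 of 73 in the pilot and 16–23% in the literature.

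- 200 × 13/73 = 35.6, and 200 × 0.18 = 36. Both are within 2 of the stated 37.
- 37/200 = 18.5%, inside 16–23% (32 to 46 participants). 37 + 163 = 200.

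The expected split reproduces. The article states no alpha for these tests and no power, effect size or SD, so there is no power figure to reproduce.

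**2. Which test goes with which question.**

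| Question | Data structure | Test named in 2.13 | Fits? |
|---|---|---|---|
| Baseline difference between groups (primary) | two independent samples | Student's t or Mann–Whitney U | yes |
| Change within a group over three visits | repeated values on the same people | repeated-measures ANOVA | yes |
| Difference between groups, simple test | two independent samples, 37 and 163 | paired t or Wilcoxon signed-rank | no |
| Change within and between groups, after year 2 | repeated values, two groups | linear mixed models | yes |

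Only the third row fails. Tried on simulated vectors of 37 and 163 values, both paired tests stop because the lengths differ; the Welch t-test and Mann–Whitney U run on the same data. One-to-one pairing would leave 163 − 37 = 126 participants unused (126/200 = 63% of the cohort), and no pairing rule is given. Relatives from one family may be correlated, but that does not create one-to-one pairs across the groups.

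**3. What the corrected test can do.** Assume two-sided 0.05, a common SD of change, no dropout and independent participants.

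- Standard error of the difference in SD units: √(1/37 + 1/163) = 0.182.
- Detectable difference at 80% power: (1.960 + 0.842) × 0.182 = 0.51 SD. At 90%: (1.960 + 1.282) × 0.182 = 0.59 SD.
- Power for an assumed 0.5 SD difference is about 78% at 37 v 163, 74% at 32 v 168 and 85% at 46 v 154.

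**4. Illustration of one possible misuse.** Suppose each group were tested separately for change and the two significance results were compared. Assume two-sided 0.05, SD of change 1 in both groups, independent participants, and the same true decline d in both groups. Power of each one-sample test of change comes from the noncentral t distribution with n − 1 degrees of freedom and noncentrality d√n. The chance that exactly one group is significant is P₁₆₃(1 − P₃₇) + P₃₇(1 − P₁₆₃).

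| Common decline d (SD) | P at n = 163 | P at n = 37 | Exactly one significant |
|---|---|---|---|
| 0 | 5% | 5% | 9.5% |
| 0.10 | 25% | 9% | 29% |
| 0.20 | 72% | 22% | 62% |
| 0.25 | 89% | 32% | 64% |
| 0.30 | 97% | 43% | 57% |
| 0.40 | 99.9% | 66% | 34% |
| 0.50 | about 100% | 84% | 16% |

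At d = 0.25: 0.887 × (1 − 0.316) + 0.316 × (1 − 0.887) = 0.607 + 0.036 = 0.64. Most of the disagreement is the larger group reaching significance alone, although the groups do not differ in change. The figure peaks near 0.25 SD and is far smaller at either end of the range.

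**The case against.** The strongest reply is that the objective already has a sound method. The next sentence of section 2.13 plans linear mixed models within and between both groups, and such a model compares change using all participants. Follow-up lasts two years, so after year 2 simply means once follow-up is complete, and nothing excludes the year-1 visit from the model. This stands. A reader might infer from the paired-test wording that the between-group question cannot be answered at all; the document does not support that. What the model leaves uncovered is the simple between-group test, including any separate comparison made at year 1. The article also does not say which result takes precedence when both are available.

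A second reply is that an analyst would notice the mismatch and use the independent-sample tests already named for the same groups in the primary objective. That is the likeliest outcome, and swapped or garbled labels are the simplest explanation. It is a reason to correct the sentence, since it relies on the analyst departing from the stated rule.

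A reader might also infer that conclusions will be drawn by comparing which group is significant, or by forcing 37 pairs. No section plans either, and within-group change is assigned to repeated-measures ANOVA. The table of discordance therefore shows what such a shortcut would cost. It does not forecast the trial's results.

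Could the paired tests have been meant for two visits within a group? The sentence sets between groups against within the same group, so the text does not say so. On that reading it would name no simple between-group test, although section 2.1 asks for a between-group analysis. Either way the sentence needs correcting.

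**Conclusion.** Wrong as written, of moderate severity. Section 2.13 assigns paired tests to a comparison of two unmatched groups, expected at 37 and 163, and those tests are invalid for it. This follows from sections 2.4, 2.12 and 2.13 alone and needs no assumption.

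The consequence is limited. It concerns a secondary objective; the primary analysis, the expected group sizes and the data collection are untouched, and the mixed models give a valid between-group comparison. The gap is the simple between-group test, at year 1 in particular. The discordance of 16% to 64% for declines of 0.10 to 0.50 SD rests on an assumed alpha, equal SDs, independent participants and a misuse that the article does not plan, so it should not be read as an expected error rate.

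**What to change.** Rewrite the sentence in section 2.13 so that each test matches its question:

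- **Within-group change:** paired t-test or Wilcoxon signed-rank test for two visits; repeated-measures ANOVA for three.
- **Between-group difference in change at years 1 and 2:** preferably the group-by-visit contrast, with confidence interval, from the linear mixed model already planned; otherwise an independent-sample test of the individual changes (Welch t-test or Mann–Whitney U).
- **Inference:** state that any claim of a difference between the groups rests on that between-group contrast, and not on one group being significant and the other not.

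The cost is one or two sentences in the analysis section or the statistical analysis plan, settled before the follow-up data are analysed. No new data, visits or participants are needed.
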